##### Intrusive memory diary (days 0–5)

Following completion of the cognitive tasks, participants are provided with a definition of intrusive memories and instructions for completing the intrusive memory diary. The diary is completed online, accessible via smartphone, or computer. There are a total of seven questions, including the date and time of the intrusion, the type (eg, image, sound, thought(s)), content of the intrusive memory, whether the intrusive memory was triggered, and level of distress and vividness rating. This diary was based on an online diary used in a trauma film study by Zeng et al. (2021) [13].

An email with the intrusive memory diary link is sent to participants as soon as they leave the lab on day 0. Participants are instructed to complete the diary as soon as possible following the experience of an intrusive memory, completing this as many times as needed. A reminder with the intrusive memory diary link is also sent via text message to participants each evening (between 1 and 3 h prior to scheduled bedtime, based on the previous week), beginning the first evening following the lab session. Participants are instructed to fill out the diary at the end of the evening after receiving the text reminder, even if they have not experienced an intrusive memory. Participants can select an N/A option to each of the diary questions, reducing demand characteristics to report an intrusive memory even if one did not occur. Thus, participants complete the diary a minimum of six times. The primary outcomes from the intrusive memory diary are the total number of intrusive memories following the lab session and number of intrusive memories each day. Secondary outcomes include examining level of distress ratings (1 = not at all distressed, 9 = extremely distressed) when intrusive memories occur.

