##### Post-lab session tasks (days 1–5)

For the 5 days following the lab session, participants complete daily intrusive memory diaries and daily mind-wandering task. Participants are instructed to complete the mind wandering task between the hours of 14:00 and 17:00 each day in a quiet environment. Participants are reminded via text and email each day at 13:55 to complete this task. They are required to complete this task on a computer or laptop with a hard keyboard. The recognition task is repeated once on day 5, with an instruction to complete this in a dark room or after sunset to ensure they can clearly view the images. Participants are instructed to complete the recognition task on a computer screen (rather than a smartphone) and are reminded via text and email on day 5. The links to the recognition task on day 5 and the mind wandering task each day are included in the reminder email. Figure 2 details the schedule of enrolment, study questionnaires, and tasks.

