## Analytic strategies

All analyses will be conducted in R.

Aim 1: The effect of a daytime nap (vs wake) on total intrusive memory frequency will be analyzed with a generalized linear mixed-effects model. Sex and day will be included as covariates. A random intercept for participant will be included to account for repeated measures across days.

Aim 2: The effect of sleep-related memory consolidation on intrusive memory frequency will be analyzed with regression and mediation analysis. Specifically, Hypothesis 2a (a nap will lead to greater recognition memory for the trauma film) will be examined with multiple regression, whereby recognition memory immediately after the nap/wake will be predicted by Condition. For Hypothesis 2b (recognition memory will mediate the relationship between sleep and intrusive memories), we will utilize mediation analysis, with Condition as the explanatory variable, recognition memory immediately after the nap/wake as the mediator, and total number of reported intrusive memories as the dependent variable. A Monte Carlo power analysis was conducted for the mediation model. A sample size of *n* = 114 has limited power to detect the indirect effect. Nonetheless, given the strong theoretical rationale for the mediation analysis and the value for future research in determining effect sizes, we will conduct the analysis and consider Hypothesis 2b as a secondary analysis. We will report effect sizes and confidence intervals of each path. We will also conduct parallel exploratory analyses for both Hypotheses 2a and 2b, utilizing recognition memory on day 5, rather than memory immediately following the nap/wake. This will explore the role of longer-delay memory consolidation on intrusive memory. Note, Hypothesis 2b may appear dependent on the success of Aim 1.

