Aim 3: The effect of overnight sleep on next-day mind wandering and intrusive memory frequency will be analyzed with mixed models. In two separate analyses, Hypothesis 3a (reduced sleep will be associated with increased mind wandering and increased intrusive memories the next day) will use sleep (total sleep time, sleep efficiency) each night to predict frequency of mind wandering and number of intrusions the next day. Hypothesis 3b (mind wandering will mediate the relationship between sleep and intrusive memories the next day) will be tested with two mediation analyses. Sleep duration each night will serve as the explanatory variable, mind wandering the next day will serve as the mediator, and number of intrusions the next day will be the dependent variable. Hypothesis 3b is also considered a secondary analysis. We were unable to perform a power analysis for this mediation as there are no previous studies examining the effect of sleep on both spontaneous cognition and intrusive memories, and thus, no basis for estimating effects sizes. If this mediation model is significant, as an exploratory analysis, we will also run a moderated mediation to explore if Condition moderates the relationship between mind wandering and intrusive memories, in the context of the mediation analysis. A separate set of models with sleep efficiency as the explanatory variable will also be run as an exploratory analysis. If the structure of the data (eg, excessive zero counts in the intrusive memory data) does not allow for mediation, alternative analytical strategies will be developed to address the same aim for Hypotheses 2b and 3b.

For Hypothesis 1 and Hypothesis 3a, we will run additional secondary analyses to examine the influence of trait mind wandering, mindful attention, frequency of intrusive thoughts, perseverative thinking and maladaptive daydreaming on the relationship between sleep and intrusive memories. Each trait measure will be examined in a separate model, where the given trait measure is added to the primary model for Hypotheses 1 or 3a. We will examine the main effect of the trait measure, as well as the interaction between the trait measures and the primary effect of interest for each model. These analyses will allow us to determine if trait factors theoretically related to the vulnerability to intrusive memory or mind wandering influence the sleep effect.

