### Data exclusion

All participants who complete the study will be included in the analysis, except as specified below. Data will not be imputed for the primary outcomes in this study. We will use sufficiently robust statistical models that accommodate missing data. Prior to the lab testing session (day 0), participants will be excluded if they have not adhered to at least five nights of the assigned sleep schedule and/or not adhered to the assigned sleep schedule for the two nights prior to the testing session. Participants are excluded from the study if they wake 30 min after their scheduled wake time on day 0. Participants are also excluded from the study if they do not follow the sleep schedule (or nap) following the lab session on day 0. For questionnaires assessing spontaneous cognition completed during PSG set-up on day 0, we may impute data for any missing responses using multiple imputation.

For the mind wandering task, for any given aim, participants will be included if they provide at least 1 day’s worth of data for that aim. We will exclude data where the participant has not understood the task or is not a conscientious responder (operationalized as below 50 per cent performance on both Go and NoGo trials). Participant understanding of the task will also be checked during a debrief at the end of the study. Timing of the mind wandering task is checked against sleep diary data, participant phone calls (regarding sleep and wake timing) and actigraphy data. If the task is completed more than 12 h post-wake time, data for that day will be excluded.

If participants report that they did not pay sufficient attention to the most graphic sections of either film and they are not observed to be watching the screen at least 80 per cent of the time, their data for the whole duration of the study will be excluded. For the intrusive memory diary, data will not be imputed. Only intrusive memories of the films are included. Unclear diary entries are discussed with participants during the debrief meeting at the end of the study. If the participant does not complete the intrusive memory diary for the entire duration of the study, their data will be excluded. We will not exclude participants who report a high number of intrusions, instead winzorization will be performed for outliers.

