### Exploratory analyses

Several exploratory analyses will also be conducted in this study. Specific examples include: (1) The influence of sex on intrusive memory frequency will be examined, as some evidence suggests females experience more frequent intrusive memories following actual [66] and analog [67] trauma exposure during certain phases of the menstrual cycle. (2) In the day-to-day analysis, we will analyze the effect of accumulation of sleep over multiple days on mind wandering and intrusive memory frequency. (3) We will further expand the temporal aspects of the model in Hypothesis 3 to include sleep the night before the lab session (night −1, day 0), to examine sleep’s effect on mind wandering and intrusive memories over a 6-day period. (4) The effect of the nap on mind wandering and intrusive memories on day 0 will also be examined. (5) A further outcome of the mind wandering task will be how many reports of mind wandering are related to the film.

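### H3b's mediator is measured part-way through its outcome window, and the exploratory day-5 version of H2b places the mediator after at least five of the six diary days

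*Protocol article*

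**What the plan says.** All references are to the Protocol article.

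- **H3b, variables** (Analytic strategies, Aim 3). Sleep on a given night is the exposure. For the rest, "mind wandering the next day will serve as the mediator, and number of intrusions the next day will be the dependent variable". The analysis is declared secondary.
- **H3b, timing of the mediator** (Post-lab session tasks). "Participants are instructed to complete the mind wandering task between the hours of 14:00 and 17:00 each day in a quiet environment". A late task is tolerated up to a limit (Data exclusion): "If the task is completed more than 12 h post-wake time, data for that day will be excluded".
- **Outcome** (Intrusive memory diary). The primary diary outcomes are the "total number of intrusive memories following the lab session and number of intrusive memories each day". The article does not restrict the H3b count to intrusions after the task, although the diary records when each one happened: "There are a total of seven questions, including the date and time of the intrusion".
- **H2b, main analysis** (Analytic strategies, Aim 2). The mediator is recognition tested on day 0, straight after the nap or wake period. Diary instructions are given only once that task is done. H2b is also declared secondary, with limited power acknowledged.
- **H2b, day-5 version** (same section). "We will also conduct parallel exploratory analyses for both Hypotheses 2a and 2b, utilizing recognition memory on day 5". That task is taken on the final day, in darkness or once the sun has set (Post-lab session tasks).
- **Content of mind wandering** (Exploratory analyses). A further outcome is "how many reports of mind wandering are related to the film".

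**The concern.** The mechanism is directional. The Introduction proposes that poor sleep increases spontaneous cognition, which then brings trauma memories into awareness. An indirect effect can support that only if the mediator precedes the outcome that it is supposed to change.

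In H3b, intrusions between waking and the afternoon task are counted in the outcome but happen before the mediator is measured. A participant who has been troubled by the film all morning may be more off-task at 15:00. The model as written would credit that association to mind wandering causing intrusions.

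In the day-5 version of H2b, almost the whole outcome has accrued before recognition is tested. Intrusions may act as rehearsal of the film and so change recognition, which would be the opposite path.

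The mechanism is the study's stated contribution (Abstract; Aims and hypotheses), so the reading of these two analyses matters even though neither is primary.

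**Working it through.** The article gives no figure of its own on this point. The check is clock arithmetic on its stated times, then a simulation under assumptions that are not in the article.

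**1. Inputs.** Task time t = 14:00 to 17:00 (Post-lab session tasks). Latest accepted time: wake + 12 h (Data exclusion). Wake w = 06:00 to 09:00 and bed b = 22:00 to 01:00 (Sleep schedule adherence). These limits describe the assigned schedule. Four of the five post-lab nights are unscheduled, so real days may differ.

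**2. Share of the H3b outcome window before the mediator** = (t − w)/(b − w).

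| Wake–bed | Task 14:00 | Task 17:00 |
|---|---|---|
| 06:00–22:00 (16 h) | 8/16 = 50% | 11/16 = 69% |
| 08:00–24:00 (16 h) | 6/16 = 37.5% | 9/16 = 56% |
| 09:00–01:00 (16 h) | 5/16 = 31% | 8/16 = 50% |

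At the 12 h limit the share of a 16 h day is 12/16 = 75%. These are shares of waking time. They are shares of intrusions only if intrusions are spread evenly over the day.

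**3. H2b, day-5 version.** The diary covers days 0 to 5, six days. Days 0 to 4 (five of six) lie wholly before the day-5 task, and so does most of day 5 if the task is done after sunset.

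**4. H2b, main version.** Recognition precedes the diary instructions, so none of the diary outcome comes before the mediator.

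**5. Simulation of H3b with no true effect of mind wandering on later intrusions.** Assumptions: 114 people over 5 days, a mean of 0.8 intrusions per day, a sleep effect on mind wandering of −0.2 SD, and 37.5–56% of intrusions before the task. Analysis: within-person linear regression, cluster-robust standard errors, both paths significant at 5%, 1,000 runs per setting.

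| Rise in mind wandering per pre-task intrusion (assumed) | False-positive mediation, whole-day count | False-positive mediation, post-task count |
|---|---|---|
| 0 | 5.0–5.2% | 5.2–6.1% |
| 0.1 SD | 12.8–22.6% | 5.5–5.8% |
| 0.2 SD | 32.9–59.6% | 6.0–6.7% |
| 0.3 SD | 58.3–88.9% | 4.8–7.0% |

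Morning and later intrusions were drawn independently given person and day. If some days are simply worse than others for a participant, the post-task count would not remove all of the bias.

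**6. Simulation of the day-5 version with no true mediation.** Assumptions: 57 per group, and a nap-group intrusion mean 0.55 times that of the wake group. If intrusions shift day-5 d-prime by 0, 0.2, 0.3 or 0.4 SD per SD of intrusions, a mediated effect is declared in 0.3%, 4%, 13% and 20% of 2,000 runs. The corresponding rate for a day-0 mediator that affects nothing was 2.5–3.5%.

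**The case against.** **The task samples a daily state.** The proposed mechanism is executive control as a consequence of sleep. The afternoon task can be read as one sample of a state set the night before, with sleep clearly first. This is a fair account of why the design was chosen. It does not answer the point, because the sample is still taken after many of the counted intrusions, and they can affect it.

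**The analyses are secondary or exploratory.** This stands, and it limits the consequence. H1, H2a and H3a do not depend on the mediation models. The exploratory label on the day-5 version does not restore the time order that mediation needs.

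**Stronger readings that the article does not support:**

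- A reader might infer that all the mediation analyses are reversed. They are not: the main H2b analysis is correctly ordered.
- A reader might infer that the H3b mediator follows its outcome. It falls inside the window, and about a third to two thirds of the waking day is still to come.
- A reader might infer that film-related off-task reports and diary intrusions are the same events. The article shows that mind wandering can be about the film, so overlap is possible. But intrusions come from a separate self-completed diary, and nothing says that a probe response becomes a diary entry.
- A reader might infer that the b path is certainly inflated. With no reverse effect the whole-day analysis keeps its error rate at about 5%.

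**Conclusion.** The concern holds for H3b and for the exploratory day-5 version of H2b only. In H3b, roughly one third to two thirds of the outcome window (31–69%, assuming 16 h awake and the protocol's sleep limits) precedes the mediator, and 75% does if the task is done at the 12 h limit. In the day-5 version, at least five of the six diary days do.

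The time order follows from the article's own wording. The size of any bias does not: the inflated error rates rest on assumed reverse effects and an assumed intrusion rate. The safe conclusion is that neither analysis, as specified, can distinguish the proposed direction from its reverse. The article specifies the variables itself, so this is not detail left to a fuller plan. The change is advisable and concerns secondary and exploratory results.

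**What to change.** **H3b.** Define the outcome as intrusions time-stamped from task completion to bedtime that day. Diary times, task times and sleep times are already collected. The window runs from 5 h (17:00 to 22:00) to 11 h (14:00 to 01:00), so include its log length as an offset. Keep the whole-day count as a sensitivity analysis and describe it as associational. Stop the window at bedtime: running it to the next task would span another night of sleep and mix two exposures.

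**Sensitivity analyses only.** (a) Adjust for intrusions earlier that day. They are downstream of the previous night's sleep, so adjustment may remove part of the effect under study. (b) Exclude film-related off-task reports from the mediator. This may discard the very lapses of control that the hypothesis concerns.

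**Day-5 recognition.** Keep the H2a-type analysis with it as an outcome. Report its relation to intrusions as an association, not as mediation. Leave the main H2b analysis as it is.

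**Cost.** Only the analysis wording changes, with no new data. Fewer intrusions are counted, so H3b intervals widen and zero counts become more common. Some times may be recalled at the evening reminder rather than logged at the event. That blurs the split at task time and should be stated as a limitation.

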### Participants and recruitment

#### Sample size

Our target sample size is 114 participants, with 57 in each condition. This study is powered primarily on Hypothesis 1, the group effect (nap vs. wake) on intrusive memory frequency. Relevant effect sizes were derived from a variety of prior studies, which have also been reported within at least one of four meta-analyses. Previous studies [14, 15, 25] examining the effect of a nap compared to wake on intrusion frequency have detected small to medium effect sizes (Hedges’ *g* = 0.38 [26] and 0.69 [15]) for between-group differences in intrusive memory frequency in the days following the experimental manipulation. Gvozdanovic et al. (2023) [14] also found a nap led to significantly fewer intrusive memories than the wake group, however, an effect size was not provided. For studies examining recognition memory for the trauma film following overnight sleep compared to wake or partial sleep deprivation [13, 23, 40], we calculated a sample size weighted average for Cohen’s *d*, finding a medium effect size of 0.5 for between-group differences where sleep, relative to wake, led to improved recognition memory for the film. Consistent with these studies, to detect a medium effect size of 0.5, with a two-tailed α of 0.05 and 80 per cent power, 57 participants are needed per group (114 participants in total) [41].

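### The exploratory test of whether Condition moderates the mind-wandering-to-intrusions path is run only if an apparently arm-averaged mediation is significant, which is a different null

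*Protocol article*

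**What the plan says.** The relevant text is the Aim 3 part of Analytic strategies in the protocol article. For Hypothesis 3b, "Sleep duration each night will serve as the explanatory variable, mind wandering the next day will serve as the mediator", with next-day intrusions as the outcome. Condition is not named in that model. On its status: "Hypothesis 3b is also considered a secondary analysis". On its power: "We were unable to perform a power analysis for this mediation as there are no previous studies", and the authors add that there is "no basis for estimating effects sizes".

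The follow-up is then made conditional: "If this mediation model is significant, as an exploratory analysis, we will also run a moderated mediation to explore if Condition moderates". The rest of that sentence gives the target of the moderation, which is the second path, from mind wandering to intrusions, examined within the mediation model.

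Other analyses in the same section carry no such condition. The models with sleep efficiency as explanatory variable, and the interactions of each trait measure with the primary effects of H1 and H3a, are planned regardless of any other result. Under Aim 2, H2b is to be run despite acknowledged limited power, partly so that effect sizes are available to later studies.

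**The concern.** A screening test should bear on the question it screens. Here the screen is the indirect effect through mind wandering, apparently averaged over arms. The question behind it is whether the second half of that pathway differs between arms. An average of zero does not imply a difference of zero. If mind wandering leads to intrusions only in the wake arm, the average path is half the wake-arm path. If the signs differ, the average shrinks further.

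What is at stake is modest but relevant to a study of mechanism. A pathway operating in one arm could be diluted in the averaged model, and the analysis that would show this would then not be run. Because the protocol could not compute power for H3b, there is no assurance that the gate would usually open.

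**Working it through.** **No plan figure to reproduce.** The protocol gives no power or effect size for H3b or its follow-up. All effects below are assumptions, in standard-deviation units.

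**Inputs from the protocol.** "Our target sample size is 114 participants, with 57 in each condition" (Sample size). There are 5 days of diary and mind wandering task (Post-lab session tasks). Person-days: 114 x 5 = 570.

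**Assumptions.** Daily residuals are independent, models are linear, data are complete and tests are two-sided at 0.05. The gate is open when both the first path (a, sleep to mind wandering) and the arm-averaged second path (b, mind wandering to intrusions) are significant.

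**Step 1: what each test targets.** With equal arms:
- gate: a x (b_wake + b_nap)/2
- follow-up, as a difference in indirect effects: a x (b_wake - b_nap)

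Both need a. They differ in whether they use the average or the difference of the second paths.

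**Step 2: approximate power.** The standard error of a, or of the average b, is about 1/sqrt(570) = 0.042. The standard error of the difference in b is about 2/sqrt(570) = 0.084. Power is about Phi(|effect|/SE - 1.96). With balanced arms the average and the difference are close to uncorrelated, so:
- ungated: P(a) x P(difference)
- gated: P(a) x P(average) x P(difference)

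The gate therefore multiplies power by roughly the chance that the average path is significant.

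Worked case, b = 0.2 and 0: the average is 0.1 (z = 2.39, power 0.665) and the difference is 0.2 (z = 2.39, power 0.665). For a = 0.2, P(a) = 0.998, so ungated is 0.998 x 0.665 = 0.66 and gated is 0.66 x 0.665 = 0.44. For a = 0.1, P(a) = 0.665, so ungated is 0.665 x 0.665 = 0.44 and gated is 0.44 x 0.665 = 0.29.

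Worked case, b = 0.2 and -0.1: the average is 0.05 (z = 1.19, power 0.22) and the difference is 0.3 (z = 3.58, power 0.95). For a = 0.2: 0.95 ungated, 0.21 gated. For a = 0.1: 0.63 ungated, 0.14 gated.

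**Step 3: simulation, 3,000 runs per case.** Simulation agrees closely with the approximation.

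| Second paths (one arm, other arm) | a = 0.2: ungated to gated | a = 0.1, a also significant: ungated to gated |
|---|---|---|
| 0.2, 0 | 65-68% to 42-43% | 44% to 27-28% |
| 0.25, 0 | 85% to 70% | 58% to 48% |
| 0.3, 0.05 | 85% to 83% | 56-58% to 55-57% |
| 0.2, -0.1 | 95% to about 20% | 64% to 14% |

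In the right-hand column the ungated figure also requires a significant first path, because a moderated indirect effect needs one. For a = 0.2 this requirement changes almost nothing, since P(a) = 0.998.

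**Step 4: a different model.** A second simulation (2,000 runs per case) centred each variable on the person's mean and added a participant effect. At a = 0.2, ungated to gated, it gave 57% to 33% for b = 0 and 0.2; 88% to 76% for 0 and 0.3; 90% to 5% for -0.15 and 0.15; and 89% to 88% for 0.1 and 0.4. The pattern is the same: the loss is large when the average is small and negligible when both arms share a sign and the average is large.

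**The case against.** The best defence is that the planned analysis is moderated mediation, not a free-standing test of the second path: the protocol places it "the relationship between mind wandering and intrusive memories, in the context of the mediation analysis". Looking for moderation only after mediation has been shown is a familiar way to limit exploratory testing. This is an exploratory follow-up to a secondary analysis, and the protocol's list of exploratory analyses is given as examples, so an extra ungated model is not ruled out.

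Much of this stands, and it excludes several stronger readings that a reader might infer:

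- *That the first path is irrelevant to the follow-up.* It is irrelevant to whether the second path differs by arm, but not to a difference in indirect effects, which is proportional to it. With a = 0.1 and b = 0.2 and 0, the fair starting point is therefore about 44%, not the 67% of the bare interaction test.
- *That the question goes untested where moderation is strongest.* A small average closes the gate, not strong moderation. With a = 0.2 and one arm at 0, raising the other arm from 0.2 to 0.25 strengthens moderation, yet gated power rises from about 43% to 70%. The severe losses need opposite signs, which nothing in the protocol predicts.
- *That real moderation will often be missed.* How often depends wholly on assumed effects.
- *That a null H3b will be reported as no mediation in either arm.* No passage says so.
- *That selection by the gate biases the estimated difference.* With equal arms the average and the difference are nearly uncorrelated, so selection bears mainly on the average and arm-specific effects.

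The defence does not make the average a test of the difference. It also does not explain why this interaction is gated when the trait interactions in the same section are not.

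**Conclusion.** The point holds as a minor one. As written, the follow-up depends on a test of a different null, and moderation can go unexamined when the arm-averaged second path is small. Under the stated assumptions the cost ranges from almost nothing (paths 0.3 and 0.05) through roughly a third of the available power (0.2 and 0) to most of it (0.2 and -0.1).

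Two features of the gate are inferred. That it averages over arms follows from Condition not being named in H3b. That both paths must be significant is an assumption, because the protocol does not say which element of the model must be. The calculations also use linear models and complete data, whereas the protocol plans mixed models and foresees excess zeros; zero-heavy counts or missed task days would probably lower power both with and without the gate. Only an exploratory result is affected.

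**What to change.** Delete the opening conditional clause of the sentence quoted above. Fit the exploratory model with the Condition by mind wandering term whatever H3b shows. Report the arm-specific second paths, the arm-specific indirect effects and the differences between arms, each with a confidence interval, and keep the exploratory label.

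The cost is one edited sentence and one extra model on data already being collected. The small downside is one more exploratory comparison, which the existing label covers.
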